#### **10.5.6 ADDITIONAL SUB-GROUP ANALYSES**

We will conduct sub-group analyses on the primary and secondary endpoints based on age (categories: ages 15-24, 25-34, and  $\geq 35$  years).

#### **10.5.7 TABULATION OF INDIVIDUAL RESPONSE DATA**

Individual participant data will not be listed by measure or time point in the final analysis or outputs.

### **11. ETHICS/PROTECTION OF HUMAN SUBJECTS**

#### **11.1 Ethical Standard**

The investigator will ensure that this study is conducted in full conformity with Regulations for the Protection of Human Subjects of Research codified in 45 CFR Part 46, 21 CFR Part 50, 21 CFR Part 56, and/or the ICH E6.

In accordance with the Tanzanian government's national PrEP framework, which recommends PrEP use for "vulnerable adolescent girls and young women (AGYW) aged 15-24 years", we will include as potential study participants any barmaids who are aged 15 and above. We do not believe that barmaids aged under 18 should be required to obtain parental consent for legal, ethical and practical reasons. Legally, the national PrEP framework does not require parental consent for initiation among those aged 15-17; this is in alignment with the age of consent for HIV self-testing, which has been 15 since 2019. Ethically, asking for parental consent to a participate in a PrEP trial risks identifying these minors as barmaids – a somewhat stigmatized profession linked to sex work – breaking privacy. Practically, many barmaids do not

live with their families (who are often not in the same city) and as people supporting themselves through work are functionally emancipated. For all these reasons we propose to treat 15-17 year old eligible barmaids as emancipated minors who will receive the same information and informed consent forms as participants 18 years of age or older.

## **11.2 Declaration of Helsinki**

This study will be run in accordance with the principles laid out in the Declaration of Helsinki.

## **11.3 Institutional Review Board**

The protocol, informed consent form(s), recruitment materials, and all participant materials will be submitted to the Heidelberg University IRB, the MUHAS IRB and the Tanzanian National Institute for Medical Research (NIMR) for review and approval. Approval of both the protocol and the consent form must be obtained before any participant is enrolled. Any amendment to the protocol will require review and approval by both IRBs before the changes are implemented to the study. All changes to the consent form will be IRB approved; a determination will be made regarding whether previously consented participants need to be re-consented. After getting official documents for permission to conduct the study, the study investigators will seek permission to work in the given area from the responsible medical officers and governments authorities like the Regional and district administrative officers.

## **11.4 Informed Consent Process**

### **11.4.1 INFORMATION DOCUMENTS PROVIDED TO PARTICIPANTS**

Consent forms describing in detail the study agent, study procedures, and risks will be given to the participant and written documentation of informed consent is required prior to starting the intervention. The following consent materials are submitted with this protocol:

- Informed consent form for screening evaluation, interview and HTC
- Informed consent form for study participation

### **11.4.2 CONSENT PROCEDURES AND DOCUMENTATION**

Informed consent is a process that is initiated prior to the individual's agreeing to participate in the study and continues throughout the individual's study participation. Discussion of risks and possible benefits of participation will be provided to the participants and their families. All participants will be informed that PrEP has been shown to be effective in reducing the risk of getting HIV by up to 90% if taken every day as directed. Additionally, participants might benefit from HIV testing during the study period, with immediate referral to HIV treatment services in the event they test positive. Other health-related diagnosis discovered during the study will also receive immediate referral for further investigation and/or treatment, and funds for transportation to reach care will be provided. Furthermore, identified findings from the study will be shared with relevant government institutions, such as the Ministry of Health, and may lead to better provision of HIV and sexual health-related services to women working in bars. In addition to adverse effects associated with the PrEP pill discussed above (page 9, section 2.4.1: known potential risks), participants will also be informed about the time commitments associated with participation in the study.

Consent forms will be IRB-approved. The investigator will explain the research study to the participant and answer any questions that may arise. All participants will receive a verbal explanation in terms suited to their comprehension of the purposes, procedures, and potential risks of the study and of their rights as research participants. Participants will have the opportunity to carefully review the written consent form and ask questions prior to signing.

The participants should have the opportunity to think about the study prior to agreeing to participate. The participant will sign the informed consent document prior to any procedures being done specifically for the study. The consent forms will emphasize that participation in the study is voluntary. The participants may withdraw consent at any time throughout the course of the trial. In the event of a withdrawal, the participant will be asked if they agree for the researchers to analyze the information already obtained from them. If they decline, the collected information will be destroyed. A copy of the informed consent document will be given to the participants for their records if they wish to take it; alternatively they will be provided with a study contact card that does not identify the topic of the study. The rights and welfare of the participants will be protected by emphasizing to them that the quality of their medical care will not be adversely affected if they decline to participate in this study.

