## **5. STUDY ENROLLMENT AND WITHDRAWAL**

### **5.1 Participant Inclusion Criteria**

Individuals must meet all of the following criteria in order to be eligible to participate in this study:

- Identify as female and report being aged 15 years or older

- Working in a licensed bar in Ubungo Municipality Dar es Salaam Municipality(DSM) as a barmaid or server
- Provide signed and dated written informed consent
- State that they are willing to comply with all study procedures and available within DSM for the duration of the study
- Be able to take oral medication and be willing to adhere to the medication regime
- Ability to consent
- A working experience of at least 2 months
- Barmaids who have used PrEP pills consistently for six months and those who have not used PrEP will be recruited for qualitative interviews on long-acting injectable PrEP

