## 11.5 Participant and data Confidentiality

Participant confidentiality is strictly held in trust by the participating investigators and staff. This confidentiality is extended to cover testing of biological samples in addition to the clinical information relating to participants. Therefore, the study protocol, documentation, data, and all other information generated will be held in strict confidence. No information concerning the study or the data will be released to any unauthorized third party without prior written approval of the Site Investigator.

Any authorized representative of the sponsor or representatives of the IRB may inspect all documents and records required to be maintained by the investigator, including but not limited to, medical records (office, clinic, or hospital) and pharmacy records for the participants in this study. The clinical study site will permit access to such records.

The study participant's contact information will be securely stored at each clinical site for internal use during the study. At the end of the study, all records will continue to be kept in a secure location for as long a period as dictated by local IRB and Institutional regulations.

Study participant research data, which is for purposes of statistical analysis and scientific reporting, will be transmitted to and stored at the offices of the Tanzanian partner organization. This will not include the participant's contact or identifying information. Rather, individual participants and their research data will be identified by a unique study identification number. The study data entry and study management systems used by clinical sites and Tanzanian research staff will be secured and password protected. At the end of the study, all study databases will be de-identified and archived in Dar es Salaam and Heidelberg.

All data processing procedures will abide by the Basic Data Protection Ordinance (DSGVO) and the Baden-Württemberg Data Protection Act (LDSG BW).

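### Section 11.4.2 extends the consent discussion to participants' families without condition, which for 15 to 17 year olds creates the disclosure risk that section 11.1 gives as a reason for not asking parents

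*Protocol*

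**What the plan says.** Protocol section 11.4.2, on consent procedures, states: "Discussion of risks and possible benefits of participation will be provided to the participants and their families". The sentence is a plain statement of what will happen. It carries no age restriction and does not make the discussion depend on the participant's wish.

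Section 11.1 takes a position on minors: "We do not believe that barmaids aged under 18 should be required to obtain parental consent for legal, ethical and practical reasons". The ethical reason is that "asking for parental consent to a participate in a PrEP trial risks identifying these minors as barmaids", an occupation the section calls somewhat stigmatized and linked to sex work, and that this would break privacy. The practical reason includes that many barmaids do not live with their families. Those aged 15 to 17 are to be treated "as emancipated minors who will receive the same information and informed consent forms as participants 18 years of age or older". Section 5.1 makes them eligible: "Identify as female and report being aged 15 years or older".

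Three other provisions protect confidentiality for participants of any age. Section 5.3 has interviews held in private vehicles or in another private place that the barmaid proposes. Section 11.4.2 lets a participant who does not want a copy of the consent form be "provided with a study contact card that does not identify the topic of the study". Section 11.5 provides: "No information concerning the study or the data will be released to any unauthorized third party without prior written approval of the Site Investigator".

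**The concern.** Section 11 gives field staff two instructions that pull against each other. One avoids approaching a minor's parents because the approach could reveal where she works. The other has the trial's risks and benefits discussed with participants' families, and minors are participants.

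What is at stake is the participant's privacy. Eligibility is limited to women working in licensed bars, and the trial concerns HIV prevention. A relative who hears the risks and benefits of taking part can learn her occupation, that she is considered at risk of HIV, and that she may be taking PrEP. Such a disclosure cannot be taken back. There is also a compliance problem. Staff who withhold the discussion to respect 11.1 and 11.5 depart from 11.4.2 as written, and section 10.3 counts any noncompliance with the protocol as a deviation. The review boards that approve the protocol under section 11.3 are likewise given two accounts of the consent process.

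**Working it through.** No arithmetic applies, and the plan states no figure on this point. The check sets the passages side by side.

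1. **Is the family discussion conditional?** No. The sentence in 11.4.2 says that it will be provided. Nothing else in sections 11.3 to 11.5 restricts it to participants who ask for it or to adults.

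2. **Are minors exempt from 11.4.2?** No. Section 5.1 admits them from age 15. Section 11.1 says they receive the same information and the same forms as adults. No separate process for minors is described, so the sentence in 11.4.2 reaches them.

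3. **What does 11.1 treat as the risk?** Asking a parent for consent, because the request itself may identify the minor as a barmaid. The wording is of a risk, it is given for ages 15 to 17, and it stands beside a legal and a practical reason.

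4. **Does a family discussion carry the same risk?** In substance, yes. A request for consent identifies the minor because the parent learns that she is being invited into a PrEP trial of barmaids. A discussion of the trial's risks and benefits tells the family the same thing, whether or not a signature is sought. This step is an inference from the content of the discussion; 11.1 does not say it.

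5. **What about adults?** The argument in 11.1 does not cover them. The tension is with private interviewing (5.3), the topic-neutral contact card (11.4.2) and the confidentiality rule (11.5). Each fits family involvement that the participant chooses, but fits poorly with involvement that is promised for every participant.

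6. **How many are affected?** Read literally, the sentence covers every participant: 160 women are to be enrolled and 1,204 screened (section 5.3). The stronger form of the conflict covers only those aged 15 to 17, and the protocol does not give that number.

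**The case against.** The best defence is that the sentence is general consent wording that no procedure puts into effect. The steps actually laid out address the participant alone: later in 11.4.2 the investigator explains the study to her and she signs, and sections 7.3.1 and 7.3.2 take consent only from her. No visit includes a family meeting and no family contact details are collected. Nothing says that staff would approach relatives against her wishes, and a relative whom she brings herself need not be an unauthorized third party under 11.5. The consent forms listed in 11.4.1 are not available for this review, so what women are told about family involvement is unknown.

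Most of this stands. It makes routine contact with families unlikely, and it shows that the two texts could be read together if family involvement were the participant's choice. But 11.4.2 does not say that it is her choice. The sentence is current text, and staff or a monitor may apply it as written.

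A reader might also infer that the wording would deter women from starting PrEP and so disturb primary endpoint 1, particularly in the youngest age subgroup. The documents do not support this. No passage links family discussion to initiation, the consent text is the same in both arms, so no difference between arms follows from it directly, and the youngest subgroup in section 10.5.6 is 15 to 24, most of which is adult. A reader might further infer that 11.1 objects to all contact with families at any age. It speaks only of asking for parental consent at ages 15 to 17.

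**Conclusion.** The sentence in 11.4.2 is wrong as written. Followed literally, it creates for participants aged 15 to 17 the same disclosure risk that section 11.1 gives as a reason for not seeking parental consent, and nothing in the protocol limits it. For adults it sits badly with the confidentiality safeguards, which is a weaker inconsistency.

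The conclusion rests on two readings: that minors go through the 11.4.2 process, which 11.1 supports directly, and that discussing the trial with a family reveals what a request for consent would reveal. It does not assume that such discussions will be common. The weight of the point is protection of participants and consistency of the protocol. It gives no ground for doubting the comparison between arms, and its extent among minors cannot be stated from the documents.

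**What to change.** Delete the three closing words of the sentence in 11.4.2, so that the discussion is with the participant only. Alternatively, keep a reference to families and state that family members are involved only at the participant's own request. Align the result with 11.1 and 11.5, and check the consent forms for matching wording.

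Any added sentence should be confined to family members. A blanket statement that nobody but the participant learns of her participation would contradict other parts of the protocol: the peer navigators who escort women to facilities and the PrEP Champion groups (section 4.1), notification of the facility or community PrEP lead about non-responders (section 4.1), and inspection of records by sponsor or review board representatives (section 11.5).

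The cost is three words removed, or one sentence added, plus the review board approval that section 11.3 requires for any amendment. Design, sample size and analysis are unaffected.

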## 11.5 Participant and data Confidentiality

Participant confidentiality is strictly held in trust by the participating investigators and staff. This confidentiality is extended to cover testing of biological samples in addition to the clinical information relating to participants. Therefore, the study protocol, documentation, data, and all other information generated will be held in strict confidence. No information concerning the study or the data will be released to any unauthorized third party without prior written approval of the Site Investigator.

Any authorized representative of the sponsor or representatives of the IRB may inspect all documents and records required to be maintained by the investigator, including but not limited to, medical records (office, clinic, or hospital) and pharmacy records for the participants in this study. The clinical study site will permit access to such records.

The study participant's contact information will be securely stored at each clinical site for internal use during the study. At the end of the study, all records will continue to be kept in a secure location for as long a period as dictated by local IRB and Institutional regulations.

Study participant research data, which is for purposes of statistical analysis and scientific reporting, will be transmitted to and stored at the offices of the Tanzanian partner organization. This will not include the participant's contact or identifying information. Rather, individual participants and their research data will be identified by a unique study identification number. The study data entry and study management systems used by clinical sites and Tanzanian research staff will be secured and password protected. At the end of the study, all study databases will be de-identified and archived in Dar es Salaam and Heidelberg.

All data processing procedures will abide by the Basic Data Protection Ordinance (DSGVO) and the Baden-Württemberg Data Protection Act (LDSG BW).

### 11.5.1 RESEARCH USE OF STORED HUMAN SAMPLES, SPECIMENS OR DATA

- **Intended Use:** Samples and data collected under this protocol may be used to study factors relating to PrEP initiation, retention and adherence. No genetic testing will be performed.

- **Storage:** No samples will be stored after analysis. Data will be stored using codes assigned by the investigators. Data will be kept in password-protected computers. Only investigators will have access to the data.

## 11.6 Future Use of Stored Specimens

Not applicable.

## 12. PUBLICATION AND DATA SHARING POLICY

This study will be registered with ClinicalTrials.gov, a trial registry. Results of the trial will be submitted for publication in peer-reviewed journals.

## 13. STUDY ADMINISTRATION

### 13.1 STUDY LEADERSHIP

The Steering Committee will govern the conduct of the study. The Steering Committee will be composed of the study PIs and independent subject matter experts.

## 14. CONFLICT OF INTEREST POLICY

The independence of this study from any actual or perceived influence, such as by the pharmaceutical industry, is critical. Therefore any actual conflict of interest of persons who have a role in the design, conduct, analysis, publication, or any aspect of this trial will be disclosed and managed. Furthermore, persons who have a perceived conflict of interest will be required to have such conflicts managed in a way that is appropriate to their participation in the trial. The study leadership has established policies and procedures for all study group members to disclose all conflicts of interest and will establish a mechanism for the management of all reported dualities of interest.

## 15. BUDGET AND BUDGET JUSTIFICATION

See attached excel sheet.

## ANNEXES

### ANNEX 1: BUDGET AND BUDGET JUSTIFICATIONS

**Primary funder: University of Heidelberg**

**Budget currency: Euro**

Demonstrating service delivery models for effective initiation and retention on PrEP among Barmaids in Dar es Salaam  
Version 4.0 – 02 December 2022

|          | Description                                                |                      | Units /Qty | Frequency | Months | Unit cost | Total cost | LOE %AGE | Total             |
|----------|------------------------------------------------------------|----------------------|------------|-----------|--------|-----------|------------|----------|-------------------|
| A | SALARIES AND WAGES                                  |                      |            |           |        |           |            |          |                   |
| A.1      | Project Country PI                                         | [name] ni | 1          | 1         | 9      | 8.750     | 78.750     | 8%       | 6.300             |
| A.2      | Co-investigator                                            | [name]        | 1          | 1         | 9      | 7.188     | 64.692     | 6%       | 3.882             |
| A.3      | Co-investigator                                            | [name]      | 1          | 1         | 9      | 7.188     | 64.692     | 5%       | 3.235             |
| A.4      | Study coordinator                                          | TBD                  | 1          | 1         | 12     | 1.000     | 12.000     | 100%     | 12.000            |
| A.5      | Lead research assistants                                   | TBD                  | 2          | 1         | 9      | 600       | 10.800     | 100%     | 10.800            |
| A.6      | Other research assistants                                  | TBD                  | 3          | 1         | 3      | 600       | 5.400      | 100%     | 5.400             |
| A.7      | Accountant                                                 | TBD                  | 1          | 1         | 9      | 900       | 8.100      | 10%      | 810               |
|          | Subtotal Personnel                                  |                      |            |           |        |           |            |          | 42.427     |
| B | FRINGE BENEFITS                                     |                      |            |           |        |           |            |          |                   |
| B.1      |                                                            | Once                 | 1          | 6         | 1      | 450       | 2.700      | 100,0%   | 2.700             |
|          | Subtotal Fringe Benefits                            |                      |            |           |        |           |            |          | 2.700      |
| C | CONSULTANT COSTS                                    |                      |            |           |        |           |            |          |                   |
| C.1      | NACP Co-investigator                                       | Monthly              | 1          | 1         | 9      | 3.000     | 27.000     | 5%       | 1.350             |
| C.2      | Overtime allowance for clinic doctors and nurse counselors | Monthly              | 15         | 1         | 9      | 100       | 13.500     | 100%     | 13.500            |
| C.4      | Overtime allowance for Community Outreach Volunteers (COV) | Monthly              | 24         | 1         | 9      | 30        | 6.480      | 100%     | 6.480             |
|          | Subtotal Consultant Costs                           |                      |            |           |        |           |            |          | 21.330     |
| D | SUPPLIES                                            |                      |            |           |        |           |            |          |                   |
| D.1      | Laptop computer                                            | Once                 | 1          | 1         | 1      | 1.500     | 1.500      | 100%     | 1.500             |
| D.2      | Printer                                                    | Once                 | 1          | 1         | 1      | 200       | 200        | 100%     | 200               |
| D.3      | Tablets                                                    | Once                 | 6          | 1         | 1      | 300       | 1.800      | 100%     | 1.800             |
| D.4      | Office supplies                                            | Monthly              | 1          | 1         | 1      | 200       | 200        | 100%     | 200               |
| D.5      | Translation                                                | Once                 | 20         | 1         | 1      | 12        | 240        | 100%     | 240               |
| D.6      | IRB payment                                                | Once                 | 1          | 1         | 1      | 3.000     | 3.000      | 100%     | 3.000             |
| D.8      | Drug delivery bags for nurses for bar-based distribution   | Once                 | 8          | 1         | 1      | 50        | 400        | 100%     | 400               |
| D.9      | Cost of Reagents                                           | Once                 | 1          | 1         | 1      | 6.000     | 6.000      | 100%     | 6.000             |
| D9       | Costs for Lab Tests                                        | Once                 | 1          | 1         | 1      | 17.000    | 17.000     | 100%     | 17.000            |
|          | Subtotal Supplies                                   |                      |            |           |        |           |            |          | 30.340     |
| E | TRAVEL                                              |                      |            |           |        |           |            |          |                   |
| E.1      | Field travel (Vehicle Hire)                                | Monthly              | 1          | 1         | 9      | 2.000     | 18.000     | 100%     | 18.000            |
|          | Subtotal Travel                                     |                      |            |           |        |           |            |          | 18.000     |
| F | OTHER DIRECT COST                                   |                      |            |           |        |           |            |          |                   |
| F.1      | Training of interviewers                                   | Once                 | 1          | 1         | 1      | 1.300     | 1.300      | 100%     | 1.300             |
| F.2      | PrEP                                                       | Once                 | 1          | 1         | 1      | 1.460     | 1.460      | 100%     | 1.460             |
| F.3      | Training of COV                                            | Once                 | 1          | 1         | 1      | 1.200     | 1.200      | 100%     | 1.200             |
| F.4      | Payment to barmaid to recompense for lost time             | Once                 | 1.204      | 1         | 1      | 3         | 3.612      | 100%     | 3.612             |
| F.5      | Payments to bar managers for facilitation                  | Once                 | 130        | 1         | 1      | 10        | 1.300      | 100%     | 1.300             |
| F.6      | Stakeholders meetings                                      | Once                 | 1          | 1         | 1      | 2.500     | 2.500      | 100%     | 2.500             |
| F.9      | Communication (internet costs)                             | Monthly              | 11         | 1         | 9      | 15        | 1.485      | 100%     | 1.485             |
| F.10     | Tablet Programmomg and data handling                       | Once                 | 1          | 1         | 1      | 2.000     | 2.000      | 100%     | 2.000             |
| F.11     | Airtime to COV for Refill reminders                        | Monthly              | 12         | 1         | 9      | 10        | 1.080      | 100%     | 1.080             |
| F.12     | Urine Assays Clearance fees                                | Once                 | 1          | 1         | 1      | 300       | 300        | 100%     | 300               |
|          | Subtotal Other Direct Cost                          |                      |            |           |        |           |            |          | 16.237     |
| G | Bar Mapping Exercise                                | Once                 |            |           |        |           |            |          |                   |
| G.1      | Research Assistants half perdiem                           | daily                | 2          | 6         | 1      | 30        | 360        | 100%     | 360               |
|          | Halfperdiem - Government filed guides                      | daily                | 2          | 6         | 1      | 10        | 120        | 100%     | 120               |
| G.2      | Transport for RAs - Hired Bajajs                           | daily                | 2          | 6         | 1      | 25        | 300        | 100%     | 300               |
| G.3      | Transport for supervisors                                  | daily                | 1          | 6         | 1      | 50        | 300        | 100%     | 300               |
| G.4      | Stationeries & photocopying of tools                       | Once                 | 1          | 1         | 1      | 25        | 25         | 100%     | 25                |
|          | Subtotal Barmapping Costs                           |                      |            |           |        |           |            |          | 1.105      |
|          | PrEP Champion intervention                          |                      |            |           |        |           |            |          |                   |
|          | Training of PrEP champions                          |                      |            |           |        |           |            |          |                   |
|          | Venue                                                      | Daily                | 1          | 3         | 1      | 85        | 255        | 100%     | 255               |
|          | Travel and half perdiem for PrEP champions                 | Daily                | 15         | 3         | 1      | 20        | 900        | 100%     | 900               |
|          | Trainers allowances                                        | Daily                | 8          | 3         | 1      | 50        | 1.200      |          | 1.200             |
|          | Refreshments                                               | Daily                | 24         | 3         | 1      | 10        | 720        |          | 720               |
|          | Sub Total Training                                         |                      |            |           |        |           | 3.075      |          | 3.075             |
|          | Monthly salary                                      |                      |            |           |        |           |            |          |                   |
|          | Monthly Salaries for PrEP champions                        | Montly               | 15         | 1         | 9      | 120       | 16.200     |          | 16.200            |
|          | Total for PrEP champion intervention                |                      |            |           |        |           | 19.275     |          | 19.275            |
| H | Total Direct Costs                                  |                      |            |           |        |           |            |          | 151.414    |
| I | Institutional Overheads                             | Once                 | 1          | 1         | 1      | 0         |            | 100%     | 22.712,10  |
|          | [name]'s PhD qualitative Studies and stipend             | Once                 | 1          | 1         | 1      | 1         | 30.000     | 100%     | 30.000,00  |
| J | Total Costs                                         | Once                 | 1          | 1         | 1      | 1         | 1          | 1        | 204.126,10 |

